### Exclusion criteria

Prior radiotherapy to the upper abdomen.Prior other malignancy – unless disease free for at least 3 years.Medical condition unsuitable such as cardiac ischemia or cerebrovascular accident within last 6 months.Psychosocial condition unsuitable.History of sorafenib therapy within 21 days prior.

### Interventions

We will recruit patients who have incomplete response after their initial TACE. All recruited patients will be allocated randomly to the SABR or re-TACE group (Fig. 1).

**Fig. 1 Fig1:**
[figure not shown]
The study flow chart. Abbreviation: TACE, trans-arterial chemoembolization; SABR, stereotactic ablative radiotherapy; CT, computed tomography; MRI, magnetic resonance imaging. Note: The randomization will be conducted by using block-stratified method, intending to balance the patient number between groups

### Arm A, the experimental group: SABR (planned *n* = 60)

SABR, or alternatively named Stereotactic Body Radiotherapy (SBRT), is a rapidly developing modern radiotherapy technique for liver tumors [47, 48]. TrueBeam™ (Varian Medical Systems, CA, USA) will be used to deliver SABR by using an extremely conformal radiation dose distribution and rapid fall-off of the peripheral dose, leading to a large sparing of surrounding normal tissues.

To achieve high precision, Image-guided Radiotherapy (IGRT) with respiratory-gated or breath-holding technique will be combined with SABR to overcome the effect of positioning uncertainty and respiratory motion. Real-time Position Management™ (RPM) system (Varian Medical System, CA, USA), version 1.7.5, will be used when breath-holding technique cannot be conducted confidentially. A CT scanner will be used for simulation (Somatom Emotion 6, Siemens Medical Solution, Forchheim, Germany). These techniques have been reported to improve treatment precision of irradiating targets that are affected by respiratory motion, such as lung, breast, and liver tumors [49].

SABR will be delivered in 5 fractions within 2 weeks, and the prescription dose will be ranged from 35 to 50 Gy, depending on tumor size, location, and normal tissue constrains. In some situations, treatment course will be prolonged to 8–10 fractions, for example, patients with poor liver function (e.g., Child B8–9) or their tumor location near the adjacent gastrointestinal tract, diaphragm, or the central zone of the liver (i.e., ≤1.5 cm around the main portal vein). The preferred inter-fraction time interval will be 48 h.

No expansion from Gross Target Volume (GTV) to CTV will be performed for most irradiating targets, and margins to generate Plan Target Volume (PTV) from Clinical Target Volume (CTV) will be ≤10 mm. The prescribed isodose should encompass 95% of PTV but 100% of CTV.

Critical organ constrains will be obeyed according to RTOG 1112 protocol [50]. Briefly, the 0.5-cc maximum dose regions of normal structures will be as follows: stomach, duodenum, small and large bowels, < 30 Gy; esophagus, < 32 Gy; and, 5 mm around the spinal cord, < 25 Gy. Bilateral mean kidney dose should be < 10 Gy. Allowed mean liver dose (MLD, the mean dose to the liver minus all GTV) should be kept < 13 Gy (if prescribed dose is 50 Gy) and < 15 Gy (if prescribed dose is 40–45 Gy).

Although the liver is considered as an organ with parallel functional subunits, the central hepatobiliary tract (cHBT) drained into the central hilum is more likely a serial structure. A 15-mm expansion of portal veins will be used as a surrogate for cHBT, and its constrains in 5-fraction SABR will be V26 < 37 c.c. and V21 < 45 c.c., as reported previously [51].

### Arm B, the active comparator group: re-TACE (planned *n* = 60)

TACE will be conducted by using a catheter to deliver chemotherapeutic agent and embolic materials into the blood vessels that supply to the tumor. Generally the procedure time will be completed within 1–2 h, and the hospitalization course will be 3 days.

Before each TACE, laboratory data will be checked, and abdominal images will be reviewed. Treatment plan will be discussed and determined by radiologists and gastrointestinal physicians. The planned catheter-inserted site will be the groin. A guide wire will be inserted into the femoral artery. A curve Angiographic Catheters (COOK MEDICAL INC., Bloomington, USA) followed by a superselective microcatheter (Terumo®, Tokyo, Japan) will be sent to the target artery in the liver.

As the catheter approach to the target, several series of angiography will be done to identify the lesion sites. After the target site is determined, catheter will be inserted to the feeding artery branch. Chemotherapy agent (Epirubicin, 30 mg), oil-based radio-opaque contrast agent (LIPIODOL® [ethiodized oil], 5–10 ml, according to tumor size), several 1 × 1 mm Sterile Sponge (Gelfoam®), contrast (XENETIX 350 [350 mg/ml], and solution for injection 10 ml) will be mixed together and then injected to the tumor site.

Post-procedure care will be prescribed, including keeping absolute bed rest for 12 h after the procedure. The incision wound will be compressed by a 2-Kg sandbag for 4–6 h for hemostasis. The medical care team will closely monitor vital signs, pulse of the distant limb, and awareness of whether TACE-associated complication occurred, such as nausea, vomiting, and allergic reactions. Proper treatments will be provided if complication occurs.

### Assignment of interventions: randomization and allocation

Computer-generated random numbers will be used for participant allocation. Two factors will be used as stratification factors, i.e., BCLC cancer stage and level of total bilirubin. A 2-by-2 cross table will be used for randomizing and blocking: total bilirubin (< 2 versus 2–3 g/dl) and BCLC (A versus B), with a block size of 4 in each stratification.

Opaque and sealed envelopes will be used for implementing the randomization and allocation sequence. When the participants are ready to be randomized, the study investigator will pull the very next randomization envelope by sequence from the envelope file, which will be locked in secure locker. The study nurse will record associated information on the study randomization list and the participant’s case report form. Finally, the envelope will be opened to reveal the subject’s treatment assignment and second study staff will double check the envelope file in real time to verify correct treatment assignment. An inspection of envelopes will be completed by data and safety monitoring board (DSMB) during routine monitoring visit. Note that blinding in either sides (i.e., physician or participants) cannot be done because of intervention natures.

### Criteria for discontinuing or modifying allocated interventions

All participants have full rights to request discontinuing intervention in any stage of trial allocation. For patients treated with SABR, if during-RT follow-up tests suggest impairment of liver function, such as GOT/GPT > 5-fold upper limit of normal range or total bilirubin > 2.0 g/dl, irradiation dose and treatment schedule will be considered to modify for consolidating patient safety.

### Strategies to improve adherence to intervention protocols

All participants will be followed up weekly during intervention period via both outpatient department (OPD) visit and phone contact, respectively. For patients with any grade 3 toxicity of CTCAE, in-patient care with aggressive management will be recommended and provided accordingly.

### Strategies for achieving adequate participant enrolment

Several strategies will be conducted for achieving an adequate enrolment of study participants. First, IRB-approved recruitment materials, including hard copy and electronic documents, will be posted in suitable platforms of hospitals and communities. Second, enrolment messages will be announced among national-level special societies, including – but not limited – gastrointestinal, surgical oncology, internal oncology, and radiation oncology. Third, inter-institute cooperation for potential patient enrolments may be done under formal supervision of IRBs.

### Relevant concomitant care and interventions that are permitted or prohibited during the trial

For all participants, relevant concomitant care and interventions for managing medical comorbidities, such as hypertension, type II diabetes mellitus, and hepatitis B/C infection, will be permitted. Permitted targeted therapy for HCC will be allowed to be prescribed subsequently – but not concomitantly – with SABR. However, chemotherapy agents, including intra-venous or oral forms, may be prohibited before a formal agreement of investigator committee.

## Follow-up measurement, assessment and outcomes

### Timing of assessments

Participants will be recruited from Dec. 2016 to Dec. 2019. All recruited participants will be followed up according to National Comprehensive Cancer Network (NCCN) guideline [6]. Table 1 shows a follow-up schedule and checklist according to recommendation of SPIRIT 2013 [46]. Follow-up data will be collected per 3 month since the baseline till 2 years. The timing to decide treatment response will be defined at the week 6 from the date of baseline. Other clinical outcome data regarding patient survival, response rate, and treatment toxicity, will be recorded systemically by schedule.

**Table 1 Tab1:** Timeline schedule for participants: screen, intervention, and follow-up

	Screening	Baseline/Enrollment Visit 0 (V0)	Treatment visit 1 (V1)	Follow up visit 2 (V2, week 6)	Follow up visit 3 (V3, week 12)	Follow up visit 4 (V4, week 24)	Follow up visit 5 (V5, week 36)	Follow up visit 6 (V6, week 48)	Follow up visit 7 (V7, week 60)	Follow up visit 8 (V8, week 72)	Follow up visit 9 (V9, week 84)	Follow up visit 10 (V10, week 96)
Informed consent form		✓										
Randomization		✓										
Demographics	✓											
Medical history	✓											
Physical examination^a^	✓	✓	✓	✓	✓	✓	✓	✓	✓	✓	✓	✓
Vital signs	✓	✓	✓	✓	✓	✓	✓	✓	✓	✓	✓	✓
Performance status	✓	✓	✓	✓	✓	✓	✓	✓	✓	✓	✓	✓
Concomitant medications	✓	✓	✓	✓	✓	✓	✓	✓	✓	✓	✓	✓
Hemotology^b^	✓	✓	✓	✓	✓	✓	✓	✓	✓	✓	✓	✓
Serum biochemistry^c^	✓	✓	✓	✓	✓	✓	✓	✓	✓	✓	✓	✓
Hepatic disease examination^d^	✓	✓										
Abdominal CT or MRI	✓				✓		✓		✓		✓	
Whole-body CT scan						✓		✓		✓		✓
EKG (as indicated)	✓											
Fibrosis evaluation (Acoustic Radiation Force Impulse; ARFI)		✓										
Pregnancy test (urine)^e^		✓										
Adverse event evaluation			✓	✓	✓	✓	✓	✓	✓	✓	✓	✓

^a^Inclusion of physical examinations for abdominal condition, ascites, encephalopathy, body temperature, weight, height, pulse, and blood pressure

^b^Inclusion of CBC/DC, PLT, WBC classification, ANC, and PT/APTT

^c^Inclusion of AST, ALT, Albumin, alkaline phosphatase, LDH, total protein, total bilirubin, direct bilirubin, BUN, Cr, sodium ([NA^+^]), potassium ([K^+^]), AFP, GGT, INR

^d^Inclusion of HBsAg and Anti-HCV. Note that the following items are selective: HBeAg, HBeAb, HBcAg, HBV DNA, and HCV-RNA

^e^Women with childbearing potential only

Note 1: It was desirable to follow the study calendar as outlined, despite progression disease (PD). For per monthly tests, +/− 1 week was permitted, and for per 3, 6 and 12 monthly tests, +/− 2 weeks were permitted

Note 2: This table was modified from recommendation of SPIRIT 2013 [46]

Abbreviation: *CBC/DC* complete blood count/differential count, *PLT* platelet, *WBC* white blood cell, *ANC* absolute neutrophil count, *PT/APTT* prothrombin time/activated partial thromboplastin time, *AST* Aspartate Aminotransferase, *ALT* alanine aminotransferase, *LDH l*actate dehydrogenase, *BUN* blood urea nitrogen, *Cr* Creatinine, *AFP* alpha-fetoprotein, *GGT* γ-Glutamyltransferase, *INR* international normalized ratio, *HAV* hepatitis A virus, *HBsAg* hepatitis B surface antigen, *HCV* hepatitis C virus, *CT* computed tomography, *MRI* magnetic resonance imaging

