### Inclusion criteria

Several inclusion criteria will be as follows.Patients who are diagnosed with HCC via one of the following methods:radiographically typical enhancement pattern with arterial enhancement and portal or delayed washed out on triple-phase dynamic Computed Tomography (CT) or Magnetic Resonance Imaging (MRI), with or without an elevated value of alpha-fetoprotein (AFP); or,histopathological confirmation of HCC.HCC patients who are treated with initial TACE with incomplete response (i.e., partial response, stable disease, or disease progression).Age ≥ 20 years old.BCLC stage A-B and Child-Pugh score A-B.Unresectable tumors, medically inoperable status, or refusal of surgery.Clinically feasible for SABR or re-TACE.SABR can be applied within 6 weeks of registration.ECOG 0–1.Life expectancy > 3 months. Negative pregnancy. No prior treatment, except for surgical resection and radiofrequency ablation (RFA). Criteria of allowed laboratory data were as follows:hemoglobin, ≥8.0 g/dl (may be post-transfusion if clinically indicated);total bilirubin, ≤3.0 mg/dl;AST (SGOT), ≤5-fold institutional upper limit of normal range;ALT (SGPT), ≤5-fold institutional upper limit of normal range;absolute neutrophil count, ≥1000/cumm;platelet count, ≥20,000/cumm (may be post-transfusion if clinically indicated); and,prothrombin time, international normalized ratio, ≥1.7.

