## Outcome measures

### Primary outcome measure

The primary outcome measure is freedom from local progression (FFLP) [24]. FFLP will be defined as time with no in-field progressive disease. Response for target lesions will be defined according to the RECIST version 1.1 and modified RECIST (mRECIST) [52]. The target lesions should show intra-tumor arterial enhancement on contrast-enhanced CT or MRI and can be accurately measured in at least one dimension as 1 cm or more [53, 54].

Several tumor responses will be defined by two independent physicians (one hepatic-specific radiologist and one radiation oncologist): complete response (CR), total disappearance; partial response (PR), 30% decrease in single longest diameter (SLD) of contrast-enhanced part; stable disease (SD), neither partial response nor progressive disease met; and, progressive disease (PD), 20% increase of SLD or new lesion(s).

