### Secondary outcome measure

Several secondary outcomes will be measured at 1 and 2 years, as follows: (1), overall survival; (2), progression-free survival; (3), tumor response rate; and (4), toxicity. Post-intervention complete or partial response will be defined as having a tumor response. Treatment-associated toxicity will be classified according to CTCAE, v.4.03 [55]. Toxicity within 3 months after initiation of interventions will be recorded as acute toxicity. And, toxicity that developed after 3 months will be considered as late toxicity. Liver-specific toxicity including classic and non-classic radiation-induced liver disease (RILD) will also be assessed. Degree of toxicities will be documented, such as ascites (i.e., absent, mild to moderate, and severe/refractory) and encephalopathy (i.e., absent, mild [I-II], and severe [III-IV]).

Several image and laboratory studies will be conducted for assessing treatment response and toxicities. First, CT, MRI, or abdominal sonography will be done per 3 months within the first two-year follow-up, then per 6 months thereafter for another 3 years. Second, specific laboratory studies will be followed up regularly, such as AST, ALT, and Bilirubin (both total and direct; Table 1). All adverse and potential harming events will be systemically collected and then analyzed in investigator meetings. Severe adverse events will be reported to IRB within 2 weeks as the IRB-monitoring guideline.

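### Treatment response is to be decided at week 6 from baseline, but no CT or MRI is scheduled then, other sections time it differently, and a SABR patient within the rules may not have finished treatment by that date

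*Protocol article*

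**What the plan says.** **Time point.** The Timing of assessments section fixes response as follows: "The timing to decide treatment response will be defined at the week 6 from the date of baseline". In Table 1 baseline is V0, the enrolment visit at which randomisation is ticked. Treatment is a separate visit, V1.

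**Scan schedule.** In Table 1 the row "Abdominal CT or MRI" is ticked at screening and at weeks 12, 36, 60 and 84. Whole-body CT is ticked at weeks 24, 48, 72 and 96. The week-6 visit (V2) has examination, laboratory tests and adverse events, but no imaging. The notes to the table allow some latitude: "for per 3, 6 and 12 monthly tests, +/− 2 weeks were permitted".

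**How response is measured.** Under Primary outcome measure, target lesions must show "intra-tumor arterial enhancement on contrast-enhanced CT or MRI", and the response categories rest on the size of the contrast-enhanced part.

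**Other statements on timing and method.** The Secondary outcome measure section says that secondary outcomes, tumour response rate among them, are measured at 1 and 2 years. For assessing response and toxicity it states: "CT, MRI, or abdominal sonography will be done per 3 months within the first two-year follow-up".

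**Start of treatment.** One inclusion criterion reads: "SABR can be applied within 6 weeks of registration". The section on Arm A gives 5 fractions within 2 weeks, or 8–10 fractions in some situations, with a preferred gap of 48 h. The section on Arm B gives no start window for re-TACE.

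**The concern.** A rule that decides response on a given date needs a measurement on or near that date. Here the date is stated and the full schedule is printed, and they do not agree. This is therefore a conflict within the article and not a detail left to an analysis plan.

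The clock also runs from enrolment and not from treatment. If SABR can begin as late as the assessment date, some SABR patients could be judged before SABR has had any effect.

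Response rate is a secondary endpoint; the primary endpoint is freedom from local progression. Even so, the Sample size calculation section uses response rate as its only basis, and the Data monitoring and auditing section makes a response-rate difference above 30% the benefit criterion for early stopping. Neither section says at which time response is read. A monitoring board member could not tell from the article whether the criterion means week 6, the first actual scan, or 1 year.

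**Working it through.** **1. Is there a scan at week 6?** Nine of the 12 columns in Table 1 contain a CT or MRI: screening and weeks 12, 24, 36, 48, 60, 72, 84 and 96. The three without are V0, V1 and V2 (week 6). With the ±2-week window the first scan after baseline falls between weeks 12 − 2 = 10 and 12 + 2 = 14. It cannot reach week 6.

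**2. Where can a SABR patient be at week 6?** This assumes that registration and baseline are about the same date.
- Latest permitted start: week 6.
- 5 fractions within 2 weeks: ends by week 6 + 2 = 8.
- 8 fractions at 48 h: (8 − 1) × 2 = 14 days, ending at about week 8.0.
- 10 fractions at 48 h: (10 − 1) × 2 = 18 days, ending at about week 6 + 18/7 = 8.6.
- A course that takes the full 2 weeks is complete by week 6 only if it starts by week 4.

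At the nominal week-12 scan, time since the start of SABR would range from 12 − 6 = 6 weeks to 12 weeks.

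**3. The plan's own sample size.** Inputs from the Sample size calculation section: 38% with TACE alone, a 30-point increase (hence 68%), α 0.05, power 80%. The statistical section makes tests two-sided. With p̄ = 0.53 and the pooled formula,

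n = [1.96·√(2·0.53·0.47) + 0.842·√(0.38·0.62 + 0.68·0.32)]² / 0.30² = (1.383 + 0.567)² / 0.09 ≈ 42.3, so 43 per arm.

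The continuity-corrected version gives 49. The stated 46 lies between the two. Taking the 30 points below the cited SABR rate (46.6% against 76.6%) with continuity correction gives 47. The stated figure is therefore close to standard results, and 46 per arm is used below.

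**4. Illustration of late starts.** Let f be the share of the SABR arm that starts too late to show a SABR effect at the read-out, and r their response rate. Then the SABR-arm rate is p₂ = 0.68(1 − f) + r·f, and

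power = Φ{[(p₂ − 0.38)·√46 − 1.96·√(2p̄(1 − p̄))] / √(0.38·0.62 + p₂(1 − p₂))}.

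- f = 0: p₂ = 0.68; (2.035 − 1.383)/0.673 = 0.967; power 83%.
- f = 20%, r = 38%: p₂ = 0.544 + 0.076 = 0.62; (1.628 − 1.386)/0.686 = 0.352; power 64%.
- f = 20%, r = 0: p₂ = 0.544; (1.112 − 1.382)/0.695 = −0.388; power 35%.

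| f (assumed) | power if late starters respond at 38% | power if they count as non-responders |
|---|---|---|
| 0% | 83% | 83% |
| 10% | 74% | 61% |
| 20% | 64% | 35% |
| 30% | 52% | 15% |

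The documents give neither f nor r. The table shows direction and range and is not a forecast. It also assumes that no re-TACE patient is late.

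**The case against.** The case on the other side has real force on several points.

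- **Week 6 may not be the response time point that matters.** The sample size and monitoring sections name no time point, response is also to be measured at 1 and 2 years, and scans run every 12 weeks from week 12. A reader might infer that the trial is sized and stopped on week-6 response, or that response will go unmeasured. The documents support neither. What stands is that several timings are given and not reconciled.
- **The 6-week limit is an outer bound in a feasibility criterion.** It is not an expected start, and Table 1 places the treatment visit before the week-6 visit. Registration is also not defined as the same date as baseline. This stands, and it limits the point to what the rules permit.
- **No delay is known to be absent from re-TACE.** Its start window is not stated, so a bias of known size against SABR cannot be claimed.
- **A missing week-6 scan affects both arms alike.** It should not be charged to SABR alone. A reader might calculate that late starts of 20% to 40% remove 14 to 27 of the planned 30 points (68% × 0.8 = 54%; 68% × 0.6 = 41%). That holds only if every late SABR patient is a non-responder and no re-TACE patient is affected. If late starters respond at 38%, the SABR rates are 62% and 56%, a loss of 6 to 12 points.
- **Sonography is a lesser matter.** Table 1 has a CT or MRI at every 12-weekly visit from week 12. Still, the text on response assessment lists it as an alternative, and that does not fit the contrast-enhanced definition.

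None of this supplies a scan at week 6.

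**Conclusion.** The point holds as an internal inconsistency. The stated response date has no scheduled imaging, although response is defined on contrast-enhanced CT or MRI; another section gives 1 and 2 years; and sonography is listed where the definition does not allow it.

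It is also possible, within the rules, for a SABR patient to be untreated or in mid-course at week 6, provided that registration is close to baseline. How many would be, and how re-TACE compares, cannot be learned from the documents. The fall in power from about 83% to 64% or 35% at an assumed 20% of late starters is an illustration only. The stronger conclusion that response cannot be measured fairly in this trial does not follow.

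The direct effect is on a secondary endpoint. It deserves correction because the sample size and the benefit stopping criterion both use response rate without saying when it is read.

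**What to change.** 1. Define the response rate at the week-12 contrast-enhanced CT or MRI already in Table 1, counted from randomisation in both arms. Bring the Inclusion criteria, Timing of assessments, Primary outcome measure and Secondary outcome measure sections and Table 1 into line with it, including what the 1- and 2-year response measurements are meant to be.
2. State that the response read-out uses CT or MRI and not sonography.
3. Cite the same time point in the response criterion for early stopping under Data monitoring and auditing.
4. Report the time from treatment start to the response scan by arm. Week 12 from randomisation reduces the possible imbalance but does not remove it, because time since the start of SABR can still range from 6 to 12 weeks at the nominal visit.
5. The section on salvage management refers to incomplete response without a date. The sponsor must reconcile which assessment is meant; no clinical rule is proposed here.

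Cost: amendment wording and a response read-out 6 weeks later than now stated. No extra scans are needed.
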